### Sample size and recruitment

2.5

To determine the sample size for the study, we used previously published data^[9]^ showing that 5 minutes of preoxygenation with HFNC achieved a median of 406 (Q2: 362; Q3: 446) mm Hg, and 5 minutes of facemask preoxygenation achieved a median PaO_2_ of 335 (Q2: 292; Q3: 389) mm Hg. Estimated mean (SD) PaO_2_ achieved with the HFNC and simple mask are 339 (82.3) mm Hg and 405 (71.3) mm Hg, respectively. This yielded a sample size of 23 participants per group, with alpha = 0.05 and power = 0.8.^[16]^ We need 26 participants per group (total 52), after accounting for 10% screen failure. We used a program called G∗Power Version 3.1.7 (Kiel University, Germany) to calculate the sample size.

Patients will be recruited on the day before surgery, once the surgery is planned and the date is scheduled. As soon as sufficient explanation is provided and consent for clinical trials is obtained, they will be assigned to a randomized trial group. After arriving at the operating room for surgery, a monitor for general anesthesia will be started and the clinical trial will be also initiated. There will be no additional visit dates for the participants, as the clinical trial will be terminated as soon as the induction of general anesthesia is completed. Efforts will be made to screen and select the appropriate participants for clinical trials, to recruit participants, and to meet the target sample size.

### Data collection management and analysis

2.6

After the examiner or the person designated by the examiner receives approval from the institutional review board (IRB), the participants’ data will be collected. To obtain accurate data, the outcome assessors have been given sufficient training, before conducting the trial, and the case report form (CRF) includes pictures and examples for objective assessment of the airway. The collected data should be stored in the original locked location, and access to the data is available only to the responsible investigator and investigators authorized by him.

To compare data between the groups, the chi-square test or Fisher exact test will be used to assess categorical variables. Student *t* test or the Mann–Whitney *U* test will be used to analyze continuous variables, as appropriate. All data manipulations and statistical analyses will be performed using SPSS for Windows, version 21 (IBM Corp, Armonk, NY) and Stata software version 13.1 (StataCorp LP, College Station, TX). Statistical analysis for the missing data will be adjusted with an estimating equation or statistical model in the final analysis. A 2-tailed *P* value of <.05 will be considered to indicate a statistically significant difference.

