#### Common procedure applied to all subjects

2.3.3

Standard monitoring including pulse oximetry (SpO_2_), 3-lead electrocardiogram (EKG), and noninvasive blood pressure will be performed. After local anesthesia, the artery catheter will be inserted into the radial artery or dorsalis pedis artery, with simultaneously baseline ABGA (T0) monitoring. After recording the data from the ABGA and initial vital signs, preoxygenation for a given group will be performed for 5 minutes. Recording of ABGA and the vital signs will be performed at the predefined time points (T1 and T2), before anesthesia injection. Endotracheal intubation will be attempted about 2 minutes after injection of anesthetics and muscle relaxants. After confirming intubation, mechanical ventilation will be started, and the vital signs and last ABGA (T3) will be recorded. The flow diagram of all the study measures is shown in Fig. 1. If the saturation recorded by the pulse oximeter falls below 90% during the procedure, the trial will be stopped immediately. If a patient from group N experiences intolerable discomfort during the course of the trial, the flow rate will be reduced to an acceptable level and recorded. If a patient from group M experiences extreme frustration because of the tight mask, the fitting should be released slightly and record. If appropriate actions are taken for each patient and he/she does not cooperate, he/she will be excluded, even if he/she has consented to participating in the study.

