### Outcomes

2.4

The primary outcome is PaO_2_ at the predefined time points.

The secondary outcomes include patients’ discomfort, end-tidal oxygen saturation (EtO_2_) at T0 and T3, EtCO_2_ at T0 and T3, other data from ABGA (eg, PaCO_2_, pH, base excess, and HCO_3_), apnea time, SpO_2_, and other vital signs (heart rate, arterial blood pressure).

The tertiary outcomes include the patients’ upper airway condition including the modified Mallampati score, upper lip bite test, thyromental distances and the presence of a mass within the upper airway tract, indication for surgery, seniority of the anesthesiologist, the number of attempts at laryngoscopy, use of any rescue maneuvers, and performers’ (anesthesiologists) satisfaction.^[10,15]^ Apnea time is defined the period from the time of propofol injection till the tracheal tube is secured.

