## Discussion

3

Preoxygenation with an HFNC during induction of general anesthesia has recently become an appealing option to anesthesiologists.^[3,6,9–12]^ This trial primarily aims to examine the trajectory of PaO_2_ levels during the whole preoxygenation procedure before and after intubation. We expect that the preoxygenation with HFNC will prove superior to the classical method with facemask, during the preinduction period of general anesthesia. To maintain the quality of this study and arrive at a reliable conclusion, the experimental design method and the research results will go through strict quality control. We will use the CONSORT checklist for the experimental design.^[17]^ The main strength of our protocol is that the study population consists of patients with head and neck cancer, who are more likely to have a difficult airway.

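### The named PaO2 analysis leaves the baseline PaO2 unused and gives no single between-group comparison of the T1–T3 profile: a loss of efficiency and of fit to the aim, not a bias

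*Protocol article*

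**What the plan says.** - **Outcome.** Protocol article, section 2.4: "The primary outcome is PaO_2_ at the predefined time points". Section 2.3.4 defines these as T0 (baseline), T1 (2 minutes), T2 (5 minutes) and T3 (after intubation).
- **Baseline.** Section 2.3.3, which applies to all subjects, places the arterial catheter "with simultaneously baseline ABGA (T0) monitoring", before preoxygenation starts.
- **Aim.** Discussion: "This trial primarily aims to examine the trajectory of PaO_2_ levels during the whole preoxygenation procedure before and after intubation". The discussion paragraph of the Abstract says much the same. The Abstract background and section 2.1 put it differently: assess PaO2 at set times and compare the two methods.
- **Analysis.** For continuous variables, section 2.6 names Student t or Mann–Whitney U: the "test will be used to analyze continuous variables, as appropriate". It names no covariate, time term or group-by-time term for the main comparison. A model is mentioned only for missing data: "Statistical analysis for the missing data will be adjusted with an estimating equation or statistical model in the final analysis".
- **Sample size.** Section 2.5 rests on one comparison, PaO2 at 5 minutes: "This yielded a sample size of 23 participants per group, with alpha = 0.05 and power = 0.8".

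**The concern.** A t or Mann–Whitney test takes one value per patient. Two things follow.

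First, T0 PaO2 plays no part in the comparison. If T0 predicts PaO2 on oxygen, adjusting for it removes part of the residual variance. It also corrects for chance baseline imbalance, which with 23 to 26 patients per arm can be noticeable. The imbalance reaches the estimate only in proportion to the slope of outcome on T0, so this matters only as far as T0 is prognostic.

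Second, tests at T1, T2 and T3 compare levels one time at a time. They do not give one between-group comparison of the post-baseline profile, which is what a reader would expect from an aim described as a trajectory.

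At stake are some power and precision in a small trial, and a headline analysis that answers the trajectory question only piecemeal.

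**Working it through.** **Inputs**
- Section 2.5 gives: "Estimated mean (SD) PaO_2_ achieved with the HFNC and simple mask are 339 (82.3) mm Hg and 405 (71.3) mm Hg, respectively". The difference is 405 − 339 = 66 mm Hg in absolute value. The sentence attaches these means to the arms in the opposite order to the medians just before it. That is a separate matter and does not change the sample size.
- Two-sided alpha of 0.05, from section 2.6 (two-tailed P "value of <.05 will be considered to indicate a statistically significant difference"), and target power of 0.80.
- Correlation r between T0 and T2 PaO2: not in the document, so assumed over a range.

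**Step 1: reproduce the plan's figure.**
Common SD = √[(82.3² + 71.3²)/2] = 77.0. Standardized difference d = 66/77.0 = 0.857.
Power of a two-sided two-sample t test uses the noncentral t with 2n − 2 degrees of freedom and noncentrality d·√(n/2). At n = 23 per group the noncentrality is 0.857 × √11.5 = 2.91.
- n = 22 per group: power 0.793
- n = 23 per group: power 0.811
- n = 26 per group: power 0.858

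The stated 23 per group is therefore reproduced, and it is the size for an unadjusted two-sided t test at 5 minutes. Sizing and named test agree. Adding the 10% allowance gives 26, as stated.

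**Step 2: add T0 as a covariate.**
The residual SD becomes 77.0 × √(1 − r²), and one degree of freedom is lost (2n − 3 = 43 at n = 23). The unadjusted size with the same precision is about 23/(1 − r²).

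| Assumed r | Residual SD multiplier | Power at 23 per group | n per group for power 0.80 | Unadjusted n with equal precision |
|---|---|---|---|---|
| 0 | 1.000 | 0.811 | 23 | 23 |
| 0.1 | 0.995 | 0.815 | 23 | 23 |
| 0.2 | 0.980 | 0.826 | 22 | 24 |
| 0.3 | 0.954 | 0.846 | 21 | 25 |
| 0.4 | 0.917 | 0.873 | 19 | 27 |
| 0.5 | 0.866 | 0.907 | 18 | 31 |

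At r = 0 the lost degree of freedom does not show at three decimals. Up to about r = 0.2 the gain is at most 0.826 − 0.811 = 0.015 in power.

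**Step 3: which test addresses the profile.**
With T0 as covariate and T1–T3 as outcomes, the group-by-time term has 3 − 1 = 2 degrees of freedom and asks only whether the group difference varies over T1–T3. Suppose the arms differ by 66 mm Hg at all three times. Every group-by-time contrast is then 66 − 66 = 0, and that test sees nothing, although the courses from baseline clearly differ. The joint test of group and group-by-time has 1 + 2 = 3 degrees of freedom. Its null is that the adjusted difference is zero at T1, T2 and T3 together, so it detects both a constant and a changing difference.

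**The case against.** The case against is substantial, and much of it stands.

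- **The named tests are valid.** Randomization supports an unadjusted comparison, and the trial was sized for exactly that. A reader might infer that the result would be biased or the trial underpowered; the documents support neither.
- **The precision gain is assumed.** No T0–T2 correlation is given. T0 precedes oxygen delivery and T2 follows five minutes of it, so r may be low and the gain trivial. This stands, and no particular gain can be claimed.
- **A formal test of trajectories is not declared.** A reader might infer that the plan promises to test whether the curves differ and then fails to. The trajectory wording stands only in discussion text, and its verb can be met by descriptive summaries. The Abstract background, section 2.1 and section 2.4 speak of PaO2 at set times, which comparisons of level do fit. What remains is a looser fit to the aim, not a contradiction.
- **The missing-data sentence.** A reader might infer that it contradicts the t or Mann–Whitney test, which has no such equation. It can equally mean that a model is used where values are missing. It is too general to establish a conflict, and it makes no model the primary analysis.
- **The text is condensed.** Section 2.6 does not say in so many words that each time point is tested separately; that is inferred from tests that take one value per patient. Model details may lie in an unseen analysis plan. The point here concerns the method that the article does name.

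**Conclusion.** The point holds as one of efficiency and fit. The only between-group method named for PaO2 ignores a baseline value planned for every patient and offers no single comparison of the T1–T3 profile.

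The precision part depends wholly on the unreported r: power at 23 per group would rise from 0.811 to between 0.815 (r = 0.1) and 0.907 (r = 0.5), with a negligible gain below about 0.2. These figures also assume the means and SDs of section 2.5, a linear relation with T0 and a common residual variance. The profile part does not depend on r. Neither part calls the validity of the named tests or the stated sample size into question.

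**What to change.** 1. Make the primary analysis the between-group difference in PaO2 at 5 minutes (T2) with 95% CI, adjusted for T0 PaO2. T2 is the time on which the sample size rests. Use either ANCOVA at T2, or the T2 contrast from a repeated-measures model of T1–T3 with T0 PaO2, group, time and group-by-time, and a small-sample degrees-of-freedom method where the software supports it.
2. For the trajectory, use the joint test of group and group-by-time over T1–T3, reported with the adjusted difference and CI at each time. Do not rely on group-by-time alone.
3. Keep the t or Mann–Whitney test as a sensitivity analysis.

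The cost is a change of analysis wording, a little more analysis work and one degree of freedom for the covariate. No new samples, procedures or patients are needed. Recruitment is under way, but section 2.1 keeps the statisticians for the final analysis blinded, so the change can be recorded and dated before anyone compares outcomes by group. If the unseen analysis plan already specifies this, section 2.6 need only be brought into line with it.

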### Monitoring

2.7

#### Adverse events

2.7.1

The investigator should institute appropriate therapeutic and follow-up measures in accordance with good medical practices and should record them in the participant's CRF. The study does not include a data monitoring committee (DMC), but an interim analysis can be made by the investigator responsible, and it will only be made if there is a significant clinical difference between the 2 groups and significant statistical differences could lead to early termination of trial.

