#### Randomization and blinding

2.3.1

Patients will be randomly assigned to 1 of 2 groups: the M group or the N group. The randomization scheme was generated using a web-based program (http://www.randomization.com), and the sequentially numbered assignments are blinded to which group each participant is assigned until just before surgery. Although the investigator could not proceed blinded due to the nature of the trial, the participants were blinded to the group assigned. An independent outcome assessor will be assigned as an investigator. Unblinding would not be needed until data analysis.

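### An interim look triggered by the observed difference, run by the unblinded investigator with no boundary, can stop the trial while the full two-sided 0.05 is spent on one analysis

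*Protocol article*

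**What the plan says.** Section 2.7.1 (Adverse events) states that there is no data monitoring committee and that the responsible investigator may carry out an interim analysis. It gives the trigger: "it will only be made if there is a significant clinical difference between the 2 groups". It gives the possible consequence: "significant statistical differences could lead to early termination of trial". It does not say when the look happens, how many looks there may be, how large a difference triggers one, which outcome is tested, or what level counts as significant.

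Three other sections bear on this:

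- Section 2.3.1 on the person who decides: "Although the investigator could not proceed blinded due to the nature of the trial". Section 2.1 blinds the statisticians, but says so only for the final analysis.
- Section 2.6 gives one two-tailed significance level for the whole trial: a P "value of <.05 will be considered to indicate a statistically significant difference".
- Section 2.5 sizes the trial "with alpha = 0.05 and power = 0.8", which is a design with one analysis. "This yielded a sample size of 23 participants per group", raised to 26 per group (52 in all) for 10% screen failure.

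**The concern.** The trigger is the result itself. To know that the arms differ, someone has to compare them while the trial is running. Under section 2.7.1 that person is the responsible investigator, who knows the allocation and, under section 2.6, has access to the data. The look therefore takes place only when the data already favour one arm, and significance at that moment can end the trial. If the trial is not stopped, a final test follows at the full 0.05.

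Two things are at stake. First, the false-positive rate of the whole procedure is no longer the 5% that the sample size assumes. Second, a trial stopped because its interim difference was large reports an estimate that is too large on average. Both would affect how the comparison of high-flow nasal oxygen with facemask can be read.

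**Working it through.** **Inputs.** From section 2.5: means and SDs of "339 (82.3) mm Hg and 405 (71.3) mm Hg, respectively", alpha 0.05, power 0.8, and 23 per group raised to 26. From section 2.6: two-sided P<.05. Only the absolute difference between the means is used here. (The arm labels on these means run opposite to the quoted medians, which does not affect the arithmetic.)

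**Step 1: reproduce the plan's sample size.**
- Difference = 405 − 339 = 66 mm Hg.
- Common SD = √[(82.3² + 71.3²)/2] = √5928.5 = 77.0.
- Standardised difference = 66/77.0 = 0.857.
- Two-sided t test at 0.05 with 80% power: 22.37 per group, rounded up to 23.
- 23/0.9 = 25.6, rounded up to 26.

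The plan's figures are reproduced. They correspond to one test at the full 0.05, with nothing set aside for an interim look.

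**Step 2: one half-way look, by formula.** With half the information available, the interim and final statistics have correlation √0.5 = 0.707. If both are tested at |Z| > 1.96, the overall error is 1 − P(|Z₁| ≤ 1.96 and |Z₂| ≤ 1.96) = 0.083.

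**Step 3: the same and other rules, by simulation.** I simulated 200,000 trials with no true difference, SDs of 82.3 and 71.3, 26 per group, and two-sided t tests at .05 at every analysis. The protocol does not give the interim level, the size of the trigger or the number of looks. The level of .05 and each row below are therefore assumptions, chosen to show the range.

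| Rule | Overall type I error |
|---|---|
| Final analysis only | 5.0% |
| One half-way look, made only if the observed difference is at least 66 mm Hg | about 6.6% (6.5% to 6.7% over repeated runs) |
| One half-way look, unconditional | 8.4% |
| Two equally spaced looks | about 11% |
| Three equally spaced looks | about 13% |
| Test after each pair from 10 per group, only while the difference is at least 66 mm Hg | about 9.5% |
| Test after each pair from 10 per group, no trigger | about 16% |

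With 23 per group instead of 26, the second row becomes 7.2%.

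**Step 4: bias of the estimate.** At 13 per group, significance at .05 needs an observed difference of about 2.064 × 77.0 × √(2/13) = 62 mm Hg. Any trial stopped there must therefore show a difference of about that size, whatever the truth. In simulation, trials stopped at a significant half-way look report about 87 mm Hg on average when the true difference is 66, and about 75 mm Hg when it is 33.

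**Step 5: check of the remedy.** With one look at a fixed number of patients that stops only at P<0.001, and a final test at .05, the overall error cannot exceed 0.05 + 0.001 = 0.051, whatever the timing. At half-way the bivariate normal calculation gives 0.0502.

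**The case against.** The strongest reply is that the protocol never says P<.05 applies at the interim. That level stands in section 2.6 as a general threshold, and a separate analysis plan may hold an interim boundary. With a half-way boundary of P<.005 and the final test left at .05, the error would be only about 5.2%. This stands: a reader might infer that the error rate is well above 5% as a matter of fact, and the document does not support that. The inflation is conditional on the assumed level. The strictest plausible trigger gives a modest excess, and the figure near 16% needs repeated testing, whereas section 2.7.1 speaks of a single interim analysis.

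This reply does not remove the problem. The article states the trigger, the decision-maker and the consequence, so the rule is on the page and is not a detail left to another document. A boundary derived for a fixed look time does not fit a look whose timing depends on the observed difference.

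A second reply is that the sentence sits under adverse events, in a trial without a monitoring committee, and names neither PaO2 nor efficacy. It may be meant for safety. This stands in part: the purpose is unclear, and if only safety events were compared, the PaO2 error rates above would not apply directly. But the wording is not limited to harm, and stopping on a statistically significant difference between arms reads naturally as including the main comparison. It is also the only between-group stopping provision in the document, so deleting it outright could remove a safety review that was intended.

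Thirdly, both the look and the stopping are optional. That is true, but discretion held by an unblinded investigator makes the error rate harder to control. A reader might also infer that a look has already been made; nothing in the document says so.

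**Conclusion.** The point holds as a defect in a stated rule. Section 2.7.1 permits an outcome-triggered look by an unblinded investigator, with no fixed time or boundary and with the power to stop the trial, on top of a design that spends the full two-sided 0.05 once.

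If .05 is used at the interim for PaO2, every scenario computed exceeds 5%, from about 6.6% to about 16% depending on rules the protocol does not give. The exact inflation cannot be read from the document. That the procedure as written does not secure 5% can be.

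**What to change.** Amend section 2.7.1 in one of two ways:

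1. Delete the outcome-triggered efficacy look. This keeps 5% at the planned 26 per group.
2. Replace it with one look at a number of patients fixed in advance and not yet reached, run by the blinded statistician, stopping only at P<0.001, with the final test at .05. Overall error is then at most about 5.1%. Half-way would be 26 of 52 patients, but section 2.1 says recruitment began in May 2019, so that point may already have passed.

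In either case, state separately whether any group-level safety review is intended, and that it is not a test of efficacy. Because recruitment is under way, also report whether any between-group comparison has already been made, by whom and at what enrolment. A boundary set now would not correct an earlier look.

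The cost is a short amendment and the loss of the option to stop early for efficacy on an informal look. With 52 patients, and each patient's participation ending at induction, that loss is small.

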#### Ethics and dissemination

2.7.2

This study was approved by the IRB of the Asan Medical Center, Seoul, Korea (AMC IRB 2019-0275; April 11, 2019). The trial was also registered at Clinical Trial Registry (NCT03896906; April 1, 2019).

This study will be conducted according to the study plan approved by the IRB of our institute and in accordance with the GCP prescribed by the US Food and Drug Administration and ICH. We will do our best to abide by them. Written informed consent will be obtained from all participants by the investigators, before enrollment. The purpose and procedure of the examination will be explained to the participants. Only applicants who have understood the purpose and risk of the examination and completed the consent form can participate in the study. Applicants are aware that they are free to discontinue their participation any time during the study.

The study did not receive any funding, and there are no conflicts of interest. The collected data stored in the locked location can be accessed only by the responsible investigator and the authorized co-investigators. The data will be stored for 3 years after termination of this study, after which it will be thoroughly and completely destroyed. The information obtained through the data analysis will be published in the journal and widely shared.

